**Procedure**

Following the approval of Bnai-Zion Medical Center, participants will be recruited by the help of their primary medical oncology staff. Each participant will undergo two assessment sessions; administered pre and post chemotherapy. Assessments will last up to one hour and will be performed in the oncology department of Bnai-Zion Medical Center or at the participant's home, at their choice. In addition, in cases where the assessment was not completed due to time constraints, the questionnaires will be completed remotely with the participant via ZOOM. All assessments will be conducted by a qualified occupational clinic.

#

# **Statistical analysis**

# *Quantitative data analysis* will be performed by SPSS version 27. Descriptive statistics will be used to describe the study population and outcome measures. Normal distribution of the variables will be verified using Shapiro Wilk test. To compare between pre- and post-chemotherapy assessment: for normally distributed variables, paired t-tests will be used; when data are not distributed normally and scales of measurements are ordinal, non-parametric tests will be used; for the primary outcome (COPM, an ordinal scale), the Wilcoxon Signed Ranks test will be used.

# Multivariate linear regression analysis (Enter method) will be used to identify the variables that best explained daily performance (measured by COPM) pre and also post chemotherapy. Variables (e.g., cognitive self-efficacy, fatigue, emotional status, executive functioning) that will be significantly correlated to daily performance (pre / post) will be entered into the model. Scatter plots of residuals against the model data will be inspected, as well as outliers and influential data points, and the variance inflation factor for multicollinearity. All analyses will be conducted using SPSS for Windows version 25.0 (SPSS, Inc., Chicago, IL, USA).

# *Qualitative data analysis* will include participant's answers to the open questions pre and post chemotherapy. Interviews will be analyzed using the phenomenological content analysis method. Data will be coded and categorized into groups to identify major themes. Two authors will perform the text analysis inductively and undertake thick description and validation by a few participants to ensure trustworthiness (Creswell & Poth, 2016).

**Backward Digit Span (BDS; Wechsler, 1997)**

**נבדק מספר_____**

במטלה הבא את/ה מתבקש/ת לחזור בסדר הפוך על רצף הספרות הבאות:

עוצרים את המטלה כאשר יש שני X ברצף.

|  | נסיון ראשון | √ או X | נסיון שני | √ או X | סה"כ |
| --- | --- | --- | --- | --- | --- |
| א. | 83 |  | 29 |  |  |
| ב. | 475 |  | 615 |  |  |
| ג. | 2619 |  | 3852 |  |  |
| ד. | 28736 |  | 59413 |  |  |
| ה. | 624719 |  | 276391 |  |  |
| ו. | 4183627 |  | 1586937 |  |  |
| ז. | 52624197 |  | 94617385 |  |  |
|  |  |  |  | סה"כ למבחן: | |

Box & Blocks Test (BBT; Mathiowetz et al.,1985)
[figure not shown]

Color Trail Test (**CTT**; D’Elia et al., 1996)

[figure not shown]

Weekly Calendar Planning Activity (**WCPA**; Toglia, 2015)

[figure not shown]

תפקוד קוגניטיבי (גרסה 3)- FACT

לפניך רשימה של משפטים שנקבעו כחשובים על ידי אנשים שנמצאים במצב דומה לשלך. **הקף/הקיפי בעיגול, או סמן/סמני באופן אחר מספר אחד בלבד בכל שורה כדי לציין את תשובתך, תוך התייחסות ל-7 הימים האחרונים.**

|  | **תפיסת הליקויים הקוגניטיביים** | אף פעם | בערך פעם בשבוע | פעמיים עד שלוש בשבוע | כמעט כל יום | מספר פעמים ביום |
| --- | --- | --- | --- | --- | --- | --- |
| CogA1 | **יש לי קושי לגבש מחשבות** 0 | 0 | 1 | 2 | 3 | 4 |
| CogA3 | החשיבה שלי איטית 0 | 0 | 1 | 2 | 3 | 4 |
| CogC7 | יש לי קושי להתרכז 0 | 0 | 1 | 2 | 3 | 4 |
| CogM9 | יש לי קושי למצוא את הדרך למקומות מוכרים 0 | 0 | 1 | 2 | 3 | 4 |
| CogM10 | **יש לי קושי לזכור היכן הנחתי את החפצים שלי, כמו המפתחות שלי או הארנק שלי** 0 | 0 | 1 | 2 | 3 | 4 |
| CogM12 | יש לי קושי לזכור מידע חדש, כמו מספרי טלפון או הוראות פשוטות 0 | 0 | 1 | 2 | 3 | 4 |
| CogV13 | **יש לי קושי להיזכר בשם של חפץ בזמן שאני מדבר/ת עם מישהו** | 0 | 1 | 2 | 3 | 4 |
| CogV15 | **יש לי קושי למצוא את המילה הנכונה כדי להביע את עצמי** 0 | 0 | 1 | 2 | 3 | 4 |
| CogV16 | אני משתמש במילה הלא נכונה כאשר אני מתכוון לחפץ מסוים 0 | 0 | 1 | 2 | 3 | 4 |
| CogV17b | יש לי קושי לומר את מה שאני מתכוון/ת בשיחה עם אחרים 0 | 0 | 1 | 2 | 3 | 4 |
| CogF19 | אני נכנס/ת לחדר ושוכח/ת מה התכוונתי להביא או לעשות שם 0 | 0 | 1 | 2 | 3 | 4 |
| CogF23 | **אני צריך/ה להתאמץ כדי להתרכז במה שאני עושה אחרת אני עושה טעות** 0 | 0 | 1 | 2 | 3 | 4 |
| CogF24 | אני שוכח/ת את שמותיהם של אנשים מעט אחרי שהציגו לי אותם 0 | 0 | 1 | 2 | 3 | 4 |

**הקף/הקיפי בעיגול, או סמן/סמני באופן אחר מספר אחד בלבד בכל שורה כדי לציין את תשובתך, תוך התייחסות ל-7 הימים האחרונים.**

|  |  | אף פעם | בערך פעם בשבוע | פעמיים עד שלוש בשבוע | כמעט כל יום | מספר פעמים ביום |
| --- | --- | --- | --- | --- | --- | --- |
| CogF25 | התגובות שלי במצבים יומיומיים איטיות 0 | 0 | 1 | 2 | 3 | 4 |
| CogC31 | עלי להתאמץ יותר מהרגיל כדי לעקוב אחרי מה שאני עושה 0 | 0 | 1 | 2 | 3 | 4 |
| CogC32 | החשיבה שלי איטית יותר מהרגיל | 0 | 1 | 2 | 3 | 4 |
| CogC33a | עלי להתאמץ יותר מהרגיל כדי להביע את עצמי באופן ברור 0 | 0 | 1 | 2 | 3 | 4 |
| CogC33c | עלי להשתמש ברשימות כתובות לעיתים קרובות יותר מהרגיל כדי שלא אשכח דברים 0 | 0 | 1 | 2 | 3 | 4 |
| CogMT1 | **יש לי קושי לעקוב אחרי מה שאני עושה אם קוטעים אותי** 0 | 0 | 1 | 2 | 3 | 4 |
| CogMT2 | **יש לי קושי** לעבור הלוך ושוב בין משימות שונות הדורשות חשיבה 0 | 0 | 1 | 2 | 3 | 4 |

**הקף/הקיפי בעיגול, או סמן/סמני באופן אחר מספר אחד בלבד בכל שורה כדי לציין את תשובתך, תוך התייחסות ל-7 הימים האחרונים.**

|  | תפיסת היכולות הקוגניטיביות | כלל לא | **מעט** | במידה מסוימת | במידה רבה | במידה רבה  מאוד |
| --- | --- | --- | --- | --- | --- | --- |
|  |
| CogPC1 | אני מסוגל/ת להתרכז | 0 | 1 | 2 | 3 | 4 |
| CogPV1 | אני מסוגל/ת לחשוב על מילים שאני רוצה להשתמש בהן כאשר אני מדבר/ת עם מישהו | 0 | 1 | 2 | 3 | 4 |
| CogPM1 | אני מסוגל/ת לזכור דברים, כמו איפה הנחתי את המפתחות או הארנק שלי | 0 | 1 | 2 | 3 | 4 |
| CogPM2 | אני מסוגל/ת לזכור לבצע דברים, כמו לנטול תרופה או לקנות משהו שאני צריך/ה | 0 | 1 | 2 | 3 | 4 |
| CogPF1 | אני מסוגל/ת לשים לב ולעקוב אחרי מה שאני עושה בלי מאמץ נוסף | 0 | 1 | 2 | 3 | 4 |
| CogPCH1 | המח שלי חד כפי שהיה תמיד | 0 | 1 | 2 | 3 | 4 |
| CogPCH2 | הזיכרון שלי טוב כפי שהיה תמיד | 0 | 1 | 2 | 3 | 4 |
| CogPMT1 | אני מסוגל/ת לעבור הלוך וחזור בין שתי משימות הדורשות חשיבה | 0 | 1 | 2 | 3 | 4 |
| CogPMT2 | אני מסוגל/ת לעקוב אחרי מה שאני עושה גם אם מפריעים לי | 0 | 1 | 2 | 3 | 4 |

Reintegration to Normal Living index (RNL; Wood-Dauphinée et al., 1988)

[figure not shown]

[figure not shown]

**FACT Fatige**

לפניך רשימה של משפטים שנקבעו כחשובים על ידי אנשים שלוקים באותה מחלה שיש לך. **הקף/הקיפי בעיגול, או סמן/סמני באופן אחר מספר אחד בלבד בכל שורה כדי לציין את תשובתך, תוך התייחסות ל-7 הימים האחרונים.**

| במידה רבה  מאוד | במידה  רבה | במידה  מסוימת | מעט | כלל לא |  |  |
| --- | --- | --- | --- | --- | --- | --- |
| 4 | 3 | 2 | 1 | 0 | אני מרגיש/ה תשוש/ה | HI7 |
| 4 | 3 | 2 | 1 | 0 | אני מרגיש/ה חולשה בכל הגוף | HI12 |
| 4 | 3 | 2 | 1 | 0 | אני מרגיש/ה אדישות לכל דבר | An1 |
| 4 | 3 | 2 | 1 | 0 | אני חש/ה עייפות | An2 |
| 4 | 3 | 2 | 1 | 0 | קשה לי להתחיל דברים בגלל שאני עייף/ה | An3 |
| 4 | 3 | 2 | 1 | 0 | קשה לי לסיים דברים בגלל שאני עייף/ה | An4 |
| 4 | 3 | 2 | 1 | 0 | יש לי אנרגיה | An5 |
| 4 | 3 | 2 | 1 | 0 | אני מסוגל/ת לבצע את פעילויותיי הרגילות | An7 |
| 4 | 3 | 2 | 1 | 0 | אני זקוק/ה לשינה במשך היום | An8 |
| 4 | 3 | 2 | 1 | 0 | אני עייף/ה מדי כדי לאכול | An12 |
| 4 | 3 | 2 | 1 | 0 | אני צריך/ה עזרה בביצוע פעילויותיי הרגילות | An14 |
| 4 | 3 | 2 | 1 | 0 | אני מתוסכל/ת מהיותי עייף/ה מדי כדי  לבצע את הדברים שאני רוצה לעשות | An15 |
| 4 | 3 | 2 | 1 | 0 | אני נאלץ/ת להגביל את הפעילות החברתית  שלי בגלל שאני עייף/ה | An16 |

**שאלות פתוחות: הערכה מס' (1) לפני כימותרפיה – דף למילוי יחד עם הנבדק/ת**

1. תכף אעביר לך כמה אבחונים שבודקים קוגניציה.

לפני שנתחיל, האם תוכל/י לתאר איך הולך לך עם מטלות קוגניטיביות מורכבות? *האם יש משהו שאת/ה יותר או פחות אוהב/ת?*

_______________________________________________________________________________________________________________________________________________________________________________________________________________________________________________________________

_____________________________________________________________________________________ **ב. אם התשובה מעידה על קושי**

ב1. נא פרט/י מהם הקשיים? מה האתגרים? למה לא הולך? נא לפרט.

______________________________________________________________________________________________________________________________________________________________________________

_______________________________________________________________________________________

_______________________________________________________________________________________

ב2. ממה נובע/ים קשיים אלה לדעתך? נא לפרט.

____________________________________________________________________________________________________________________________________________________________________________________________________________________________________________________________________________________________________________________________________________________________

ב3. כיצד לדעתך קשיים אלה באים לידי ביטוי בתפקודך היומי? נא לפרט.

____________________________________________________________________________________________________________________________________________________________________________________________________________________________________________________________________________________________________________________________________________________

ב3. איזה עוד גורמים לדעתך משפיעים על התפקוד היומיומי שלך? נא לפרט.

____________________________________________________________________________________________________________________________________________________________________________________________________________________________________________________________________________________________________________________________________________________

**ג. אם התשובה אינה מעידה על קשיים**

ג1. איזה עוד גורמים לדעתך משפיעים על התפקוד היומיומי שלך? נא לפרט.

____________________________________________________________________________________________________________________________________________________________________________________________________________________________________________________________________________________________________________________________________________________

**שאלות פתוחות: הערכה מס' (2) אחרי כימותרפיה – דף למילוי יחד עם הנבדק/ת**

1. בדומה לפגישה הקודמת, תכף אעביר לך כמה אבחונים שבודקים קוגניציה.

לפני שנתחיל, האם תוכל/י לתאר איך הולך לך עם מטלות קוגניטיביות מורכבות? *האם יש משהו שאת/ה יותר או פחות אוהב/ת?*

_______________________________________________________________________________________________________________________________________________________________________________________________________________________________________________________________

_____________________________________________________________________________________ **ב. אם התשובה מעידה על קושי**

ב1. מהם השינויים שאת/ה חווה במצבך הקוגניטיבי? נא לפרט.

______________________________________________________________________________________________________________________________________________________________________________

_______________________________________________________________________________________

_______________________________________________________________________________________

ב2. ממה נובע/ים שינויים אלה לדעתך? נא לפרט.

____________________________________________________________________________________________________________________________________________________________________________________________________________________________________________________________________________________________________________________________________________________________

***אם לא מעלה כימותרפיה כגורם, לשאול: *יש אנשים שמדווחים על שינוי בקוגניציה בעקבות כימותרפיה. האם אתה מרגיש שינויים כאלה? אם כן נא לפרט***

*____________________________________________________________________________________________________________________________________________________________________________________________________________________________________________________________________________________________________________________________________________________________*

ב3. כיצד לדעתך שינויים אלה באים לידי ביטוי בתפקודך היומי? נא לפרט.

____________________________________________________________________________________________________________________________________________________________________________________________________________________________________________________________________________________________________________________________________________________

ב3. איזה עוד גורמים לדעתך משפיעים על התפקוד היומיומי שלך? נא לפרט.

____________________________________________________________________________________________________________________________________________________________________________________________________________________________________________________________________________________________________________________________________________________

***אם לא מעלה כימותרפיה כגורם, לשאול: יש אנשים שמדווחים על שינוי בתפקוד היומיומי בעקבות כימותרפיה. האם אתה מרגיש שינויים כאלה? אם כן נא לפרט**

**___________________________________________________________________________________________________________________________________________________________________________________________________________________________________________________________________________________________________________________________________________________________________________________________________________**

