while adhering to five rules Scores include measures of accuracy, number of appointments entered, planning time (time from the beginning of the assessment until the first appointment is scheduled), total time, efficiency (calculated from the accuracy and total time), error types, number of rules followed out of the five given, and number of strategies used.

d. Perceived cognitive executive functioning

- *Cognitive Self Efficacy* (**SE**) will be assessed by the Cognitive Self Abilities Scale CogPCA (FACT-Cognitive Function Version 3). [The](https://www.facit.org/) CogPCA scale includes 7 statements with responses given on a 5-point Likert scale (from 0, never; to 4, several times a day). The score range= 0–28 with higher scores indicating higher difficulties.

*- Perceived Cognitive Impairment* will be assessed by the Perceived Cognitive Impairment scale – PCI (FACT-Cognitive Function Version 3; Wagner et al., 2009). The PCI scale includes 18 statements with responses given on a 5-point Likert scale (from 0, never; to 4, several times a day). The score range= 0–72 with higher scores indicating higher difficulties.

*- Three open-ended questions* (pre chemo "since diagnosis" and post chemo "since treatment"). The questions regarding person's changes in cognitive functioning and the consequences of these changes on his/her daily functioning will be presented on a sheet of paper and they will be asked to write their answers bellow together with the accessor.

1. *Emotional status* will be assessed by the Emotional Well-Being subscale (EWB; Cella et al., 1993) from the FACT-G (General) questionnaire (https://www.facit.org/). The EWB scale includes six statements with responses given on a 5-point Likert scale (from 0, not at all; to 4, very much). The score range= 0–24 with higher scores indicating higher emotional deficits.
2. *Fatigue* will be assessed by the Functional Assessment of Chronic Illness Therapy – Fatigue (FACIT-F) (Version 4; <https://www.facit.org/> ). The FACT Fatigue includes 13 statements with responses given on a 5-point Likert scale (from 0, not at all; to 4, very much). The score range= 0-52 with higher scores indicating more fatigue.

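### At the post visit only, a chemotherapy cue is scripted before the cognitive tests for some participants, which can bias the pre-post comparison towards worsening

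*Protocol*

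**What the plan says.** The post-chemotherapy sheet (Appendix 1, open questions, assessment 2) opens by announcing that cognitive assessments will follow shortly, as at the previous meeting: "בדומה לפגישה הקודמת, תכף אעביר לך כמה אבחונים שבודקים קוגניציה". It then asks, before starting, how the participant manages with complex cognitive tasks: "לפני שנתחיל, האם תוכל/י לתאר איך הולך לך עם מטלות קוגניטיביות מורכבות". The pre-chemotherapy sheet opens in the same way.

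The post sheet then branches. In the branch headed "אם התשובה מעידה על קושי" (the answer indicates difficulty), item B1 asks what changes the participant experiences in their cognitive state, and B2 asks what causes them. An instruction to the assessor follows: "אם לא מעלה כימותרפיה כגורם, לשאול" (if chemotherapy is not raised as a factor, ask). The scripted text is "יש אנשים שמדווחים על שינוי בקוגניציה בעקבות כימותרפיה", with a question on whether the participant feels such changes. After the later item on other factors affecting daily function, the same instruction introduces "יש אנשים שמדווחים על שינוי בתפקוד היומיומי בעקבות כימותרפיה" (some people report a change in daily functioning after chemotherapy). The no-difficulty branch has neither prompt.

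On the pre sheet, B1 asks about difficulties rather than changes. B2 asks for their cause, "ממה נובע/ים קשיים אלה לדעתך", with no suggested answer and no follow-up about chemotherapy.

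The main text (CRF and Measures) describes three open questions about changes in cognitive functioning, anchored "pre chemo 'since diagnosis' and post chemo 'since treatment".

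**The concern.** A pre-post comparison in one group attributes the difference between visits to what happened between them. That requires measurement conditions to match at both visits. Here a cue that agrees with Hypothesis 1a (worsening after chemotherapy) is given at the second visit only, immediately before the objective tests. If it changes effort, confidence or reporting, the change falls entirely on the post-visit score. No untreated group receives the same cue, and neither the paired t-test nor the Wilcoxon test can separate it from an effect of treatment.

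The wording adds a second asymmetry. A participant whose difficulty is the same as at baseline is asked at the second visit to describe changes. That is leading even without the chemotherapy prompt, and it makes the two sets of qualitative answers less comparable.

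**Working it through.** The core of the point is a comparison of the two sheets; the protocol gives no figure to reproduce.

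**Sheets side by side**

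| Element | Pre sheet | Post sheet |
|---|---|---|
| Placed before the cognitive tests | yes | yes |
| B1 asks about | difficulties | changes |
| Open question on cause | yes | yes |
| Chemotherapy prompt, cognition | none | if difficulty is reported and chemotherapy not named |
| Chemotherapy prompt, daily function | none | same conditions |
| No-difficulty branch | no prompt | no prompt |
| Diagnosis or treatment anchor on the visible sheet | absent | absent |

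The main text does not override this order. CRF and Measures fixes a sequence only within the dual task.

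**Illustration of size**

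Inputs:
- n = 50, from Participants.
- One group and a paired t-test for normally distributed outcomes, from Study design and Statistical analysis.
- Assumed, because the protocol does not give them: two-sided alpha 0.05, no true change, a share f of participants prompted, and a shift of d in each prompted participant, in SDs of the paired difference.

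Step 1. The average shift over the whole sample is f × d.

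Step 2. The noncentrality is δ = f × d × √50, with √50 = 7.071. For f = 0.5 and d = 0.2, δ = 0.5 × 0.2 × 7.071 = 0.707.

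Step 3. The chance of a significant result in the direction of worsening is P(T > t₀.₉₇₅,₄₉), where T is noncentral t with 49 degrees of freedom and noncentrality δ. With δ = 0 this is 2.5%.

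| Share prompted f | d = 0.1 | d = 0.2 | d = 0.3 |
|---|---|---|---|
| 25% | δ = 0.177: 3.7% | δ = 0.354: 5.3% | δ = 0.530: 7.5% |
| 50% | δ = 0.354: 5.3% | δ = 0.707: 10.3% | δ = 1.061: 17.9% |

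The calculation keeps the SD of the paired difference unchanged. A shift in only part of the sample inflates the variance by 1 + f(1 − f)d². At f = 0.5 and d = 0.3 this is 1 + 0.25 × 0.09 = 1.0225, which is negligible.

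The table applies to one outcome analysed by paired t-test. The COPM is to be analysed by the Wilcoxon test, and it is not shown that the COPM follows the prompt.

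**The case against.** Several counter-arguments have force.

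- **The effect is not demonstrated.** Nothing in the protocol shows that one conditional question alters test performance. All participants know they are being assessed before and after chemotherapy, so the added suggestion may be slight. Practice on repeated tests could push the other way. This stands: the supportable claim is that the cue can bias the comparison, not that it does, and the net direction of all influences is not established.
- **Few may be prompted.** Two conditions must both be met. This stands, and it is why size is shown by share prompted. A reader might instead apply the shift to all 50 participants. Average shifts of 0.1, 0.2 and 0.3 SD would then give about 10%, 29% and 56% (normal approximation). The documents do not support that reading: if a quarter are prompted, an average of 0.3 SD needs 0.3 / 0.25 = 1.2 SD in each of them.
- **The primary outcome may be untouched.** A reader might infer that the COPM and questionnaires are contaminated too. The script says only that tests of cognition follow. The session order of the COPM and the questionnaires is not fixed, and Procedure lets unfinished questionnaires be completed later by video call. Any effect on them depends on their being collected after the prompt.
- **Some asymmetry is inherent.** A prompt about experienced effects of chemotherapy makes no sense before it is given. The pre sheet also has probes of its own in B1. Both are true, but they do not justify placing the prompt ahead of testing.
- **Prompted answers are already separable.** Each prompt follows the spontaneous question and has its own answer lines. This stands, so the qualitative damage is avoidable with the present form.
- **The assessor aid sheets are not visible.** They may carry the anchors or further instructions on order. It can be said only that the visible fill-in sheets lack the anchors. On wording, the post sheet's reference to changes agrees with the main text; the pre sheet is the one that departs from it.

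**Conclusion.** The point holds as a design weakness that is cheap to remove. The post sheet alone puts a chemotherapy cue before cognitive testing, for participants who report difficulty and do not name chemotherapy themselves. In a one-group pre-post study testing for worsening, this can bias the cognitive tests, and any self-report collected afterwards, towards the hypothesised result.

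Its size cannot be derived from the protocol. Across the assumed range (25% or 50% prompted, shift 0.1 to 0.3 SD), the chance of a false worsening on one outcome is about 4% to 18% against a nominal 2.5%. Confidence is high for the order and wording of the visible sheets. It is lower for the bias, which rests on inference from the cue. The documents do not support a claim that results will be biased, that the whole sample is exposed, or that the COPM is affected.

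**What to change.** 1. Move the two chemotherapy prompts to the very end of the post session, after all tests, questionnaires and the COPM. The rest of the sheet can stay where it is. Moving the whole sheet would be a trade-off, because the answers would then reflect the test performance just experienced.
2. Use a parallel B1 stem at both visits, carrying the anchor that CRF and Measures describes: since diagnosis at the first visit, since treatment at the second.
3. Analyse prompted attributions separately from spontaneous ones, using the separate answer lines already on the form. If post visits have already taken place with the present sheet, record which participants were prompted.

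The cost is an edit to two forms. The downside is small: the prompts are separated from the open questions they belong to, and participants may be more tired when they answer them.
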